## Abstract

**Background:**

Youth involved in the juvenile justice system (YIJJ) have high rates of substance use problems; however, rates of YIJJ engagement in substance use services is low. Barriers to service engagement include lack of appropriate screening and connection to services by the juvenile justice system, as well as lack of resources for delivering evidence-based treatment in community-based settings. To address these barriers, this paper describes a protocol for a type 1 hybrid design to (1) implement universal substance use screening for YIJJ; (2) implement and evaluate the feasibility and effectiveness of a brief, three-session substance use interventions based in motivational interviewing for youth with mild/moderate substance use: Teen Intervene (an individual-based intervention); (3) implement ENCOMPASS, an evidence-based substance use intervention based in motivational enhancement and cognitive behavioral therapy for youth with severe substance use; and (4) evaluate facilitators and barriers to implementing these interventions for mild to severe substance use among YIJJ in community mental health centers (CMHC).

**Methods/design:**

Using a hybrid type 1 clinical effectiveness-implementation design, we will collaborate with CMHCs and juvenile justice in two rural Indiana counties. Guided by the EPIS (exploration, preparation, implementation, sustainability) framework, we will measure factors that affect implementation of substance use screening in juvenile justice and implementation of substance use interventions in CMHCs utilizing self-reports and qualitative interviews with juvenile justice and CMHC staff pre- and post-implementation. YIJJ with mild/moderate substance use will receive a brief interventions and YIJJ with severe substance use will receive ENCOMPASS. We will measure the effectiveness of a brief and comprehensive intervention by assessing changes in substance use across treatment. We anticipate recruiting 160 YIJJ and their caregivers into the study. We will assess intervention outcomes utilizing baseline, 3-, and 6-month assessments.

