#### Substance use screening in the juvenile justice system

First, there is a lack of systematic mental health and substance use screening in the juvenile justice system [18]. Given the high rates of substance use and mental health problems among YIJJ, as well as the higher risk of recidivism among YIJJ with substance use and mental health problems, screening and identifying those in need of services is an important task for juvenile justice staff [6, 18–20]. Although juvenile probation officers (JPO) typically function as gatekeepers who help connect YIJJ with appropriate services, there is often a significant lag time between YIJJ’s release from detention and their first contact with a JPO, which leads to delays in service connection and engagement. Moreover, arrest and detention can be viewed as a “crisis event” for youth during which time their motivation for seeking behavioral health services is high; therefore, screening and identification of service needs and connection to services is crucial during the initial intake period following arrest [21]. Thus, we propose to implement universal substance use screening in juvenile justice settings during initial intake following arrest in order to increase identification of YIJJ in need of services and in turn increase referral and connection to appropriate services in community-based settings.

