#### Risk level determination

Based on the youth’s initial CRAFFT score as well as their scores on initial baseline measures collected after consent at the first/baseline visit, youth will be categorized as either low to mid-risk or high-risk based on criteria from the American Society of Addiction Medicine (ASAM). ASAM criteria utilizes six dimensions of an individual’s substance use and overall functioning to determine appropriate level of care [25]. We will determine risk level based on youth’s pattern of substance use, such as frequency and quantity of use, as well as problematic use based on DSM-5 substance use disorder symptoms. Table 2 describes specific risk determination criteria we will determine based on assessment. Generally, high-risk youth will be those who have identified past year repeated use of more lethal substances with a high risk for overdose and withdrawal potential (e.g., opioids, methamphetamine) and those who endorse three or more DSM-5 SUD symptoms, which is consistent with a moderate to severe SUD. All other youth initially will be randomized to one of the brief interventions. Based on preliminary data collected from each county, it is estimated that about 10% of youth will be in the high-risk group.

**Table 2 Tab2:** Risk level determination

	Brief intervention (low/mid risk)	Comprehensive intervention (high risk)
Substance use frequency	Less than weekly use of cannabis, alcohol, nicotine	Weekly or more frequent use of any substance Past year repeated use of lethal substance (opioids, methamphetamine, benzodiazepines)
Problematic substance use	Minimal problems or consequences of use ≤ 2 DSM-5 SUD symptoms	History of overdose Report of experiencing withdrawal ≥ 3 DSM-5 SUD symptoms

Following determination of risk level, high-risk youth will be assigned to complete ENCOMPASS, the comprehensive substance use treatment. Youth who are categorized as low- or mid-risk will be randomly assigned to one of the two brief interventions. Following randomization, youth will engage in either Teen Intervene or Family Check-Up with a brief intervention specialist.

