### Data analysis

#### Measurement of intervention effectiveness and treatment response

##### Preliminary analyses

Preliminary analyses will be used to compare the primary treatment response outcome (confidence of abstaining measured by the BSCQ) and substance use outcome across the responders and non-responders of the brief intervention and ENCOMPASS at baseline, 3 months, and 6 months. A separate model will be utilized to measure effectiveness among those assigned to ENCOMPASS. Substance use will be calculated as number of days in the past month of using alcohol, marijuana, and other substances (range 0–90). These outcomes will be compared between groups with longitudinal generalized linear models (GLM) using the GENMOD procedure with a linear link and normal error distribution. The BSCQ and substance use outcome will be analyzed in separate models. The baseline measure of BSCQ or substance use days will be adjusted as covariates and the repeated measurements of each outcome at 3 months and 6 months will be analyzed simultaneously in the model.

The GLMs are easily fit for non-Gaussian distributions by specifying appropriate link functions and error distributions. If substance use days exhibit sparse counts or large frequency of zeros, we will consider using logistic, Poisson, or zero-inflated Poisson regression models, depending on the observed distributions of outcome behaviors. We also will explore analyzing substance use as time-to-event data using a Cox proportional hazards regression model with the SAS PHREG procedure with censoring if loss to follow-up occurs. Effect sizes will be computed from the model as differences between groups on adjusted means divided by SDs for the linear models, or differences between odds for logistic models or hazards for Poisson models.

The median and relevant percentile (e.g. 25th or 75th) of time to events will be presented by group with associated confidence intervals. All models will include an indicator variable for whether the subject was enrolled as a detained or probation youth. Other covariates will be included based on their theoretical importance as potential confounders and on their imbalance between randomized arms at baseline. We also will examine moderators that we have hypothesized to be potential determinants of treatment response (e.g., family functioning).

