##### Analyses

The specific analyses and hypothesis tests (which are preliminary because this is a feasibility study) will assess effectiveness of the brief intervention and ENCOMPASS on substance use outcomes. These data will be used to generate hypotheses about brief and comprehensive interventions for a future larger study.

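### Change in use among ENCOMPASS youth is to be read as effectiveness, but there is no comparator and selection rests partly on baseline use, so a treatment effect cannot be separated from regression to the mean

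*Protocol article*

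**What the plan says.** The Methods/design paragraph of the abstract gives the basis for effectiveness: "We will measure the effectiveness of a brief and comprehensive intervention by assessing changes in substance use across treatment". The section Analyses says that the hypothesis tests "will assess effectiveness of the brief intervention and ENCOMPASS on substance use outcomes". Preliminary analyses adds: "A separate model will be utilized to measure effectiveness among those assigned to ENCOMPASS". No comparison group is named for that model.

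Allocation is by risk: "Following determination of risk level, high-risk youth will be assigned to complete ENCOMPASS, the comprehensive substance use treatment" (Risk level determination). Classification uses the intake CRAFFT together with "scores on initial baseline measures collected after consent at the first/baseline visit, youth will be categorized as either low to mid-risk or high-risk". The variables include the outcome construct: "We will determine risk level based on youth’s pattern of substance use, such as frequency and quantity of use". Table 2 places "Weekly or more frequent use of any substance" in the high-risk column, alongside past-year repeated use of listed drugs, overdose history, withdrawal and three or more DSM-5 symptoms. About 10% of youth are expected to be high risk.

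The outcome is past-month days of use (0 to 90). Baseline enters as a covariate, and the 3- and 6-month values are the responses. Sample size and power expects 12 ENCOMPASS and 116 brief-intervention youth with 6-month data. Analyses calls the tests preliminary. Limitations mentions neither regression to the mean nor the lack of a comparator.

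**The concern.** A group taken from the upper end of a distribution, partly on the variable that is later re-measured, is expected to score lower the second time even if nothing is done. Here the selecting measurement and the starting point of the change come from the same visit. With no high-risk group managed otherwise, nothing in the data separates that fall from a benefit of ENCOMPASS.

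Entry around an arrest is a second uncontrolled influence. The protocol writes that "arrest and detention can be viewed as a “crisis event” for youth", but in the context of motivation for services, and it does not say which way use would move. Use may decline afterwards. Equally, detained youth may have had little opportunity to use in the month before baseline, which would push the change upward.

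At stake is what the study can report about ENCOMPASS, and what it passes on to the larger study it is meant to inform. Sample size and power gives estimation of effect sizes as the goal and cites a minimum of 12 per group, which is the expected ENCOMPASS number. Preliminary analyses defines effect size for linear models as a difference between groups. The ENCOMPASS model has one group, so change from baseline is the quantity a reader would naturally reach for.

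**Working it through.** **The plan's own figures.**
- Risk split: 10% of 160 = 16, leaving 144.
- Retention: 16 × 0.8 = 12.8 (stated 12); 144 × 0.8 = 115.2 (stated 116). Both are close.
- Power: effect size 0.63, 80% power, two-sided, alpha 0.05 assumed, gives 40 per group by the normal approximation (power 0.804).
- Inflation: 1 + 39 × 0.01 = 1.39; 40 × 1.39 = 55.6, i.e. 56.

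These reproduce, but they concern responders against non-responders. No calculation in the protocol concerns ENCOMPASS change.

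**Model for selection alone.** Baseline use X is standard normal. Follow-up use is Y = rX + √(1 − r²)e, with no treatment effect and no time trend. The severity index is Z = cX + √(1 − c²)u, and the top 10% on Z go to ENCOMPASS. Both r (test-retest correlation) and c (correlation of the selection criteria with baseline use) are assumptions.

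The mean of the top 10% of a standard normal is 0.1755 / 0.10 = 1.755, so

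expected fall = c × (1 − r) × 1.755 SD.

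For c = 1 and r = 0.7 this is 0.3 × 1.755 = 0.53 SD. For c = 0.6 and r = 0.7 it is 0.6 × 0.53 = 0.32 SD.

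**Simulated chance of a significant fall** (paired t-test, two-sided 0.05, n = 12; nominal 2.5% in that direction). Each cell gives the expected fall in SD, then the chance:

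| r | c = 1 (purely on use) | c = 0.6 | c = 0.4 |
|---|---|---|---|
| 0.5 | 0.88; 88% | 0.53; 41% | 0.35; 21% |
| 0.6 | 0.70; 77% | 0.42; 34% | 0.28; 17% |
| 0.7 | 0.53; 63% | 0.32; 27% | 0.21; 14% |
| 0.8 | 0.35; 45% | 0.21; 18% | 0.14; 10% |
| 0.9 | 0.18; 24% | 0.11; 11% | 0.07; 7% |

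If selection is unrelated to the transient part of baseline use, the chance returns to about 2% to 3%. A skewed 0-to-90-day version, selected on baseline days, gave 55%, 33%, 23% and 13% at observed correlations of 0.36, 0.57, 0.69 and 0.84.

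**Brief-intervention group.** The lower 90% has mean −1.755 × 0.1 / 0.9 = −0.195. The expected rise under selection on use is (1 − r) × 0.195, i.e. 0.10, 0.06 and 0.02 SD at r = 0.5, 0.7 and 0.9. At n = 116 a significant rise appears in 19%, 13% and 7% of simulated trials.

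**With a comparator** chosen by the same rule, the expected between-group difference from this source is zero.

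**The case against.** The strongest reply has five parts.

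1. *A significant fall is not shown to be likely.* A reader might infer that it is. That needs two correlations the protocol does not give. Table 2 mixes past-year use, overdose history, withdrawal and symptoms with frequency of use, and the intake CRAFFT precedes the baseline visit, so c = 1 is an upper bound rather than a description. This stands: in the normal model the chance exceeds 50% only with strong selection on use and modest stability.

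2. *The paired test is not in the protocol.* Preliminary analyses adjusts for baseline, and the exact ENCOMPASS contrast is left open, as an article may do. This stands as a limit on the percentages. It does not rescue the inference: adjustment for baseline helps when groups are compared, and here there is one group.

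3. *The tests are preliminary and ENCOMPASS is only implemented.* The numbered aims attach evaluation of effectiveness to the brief intervention, so it is too strong to say that the study will conclude effectiveness. But the abstract, Preliminary analyses and Analyses all use the word effectiveness for ENCOMPASS. The label preliminary does not remove bias from an estimate.

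4. *Within-group effect sizes are not the stated product.* Correct; the definition given is between groups. The risk is that within-group change fills the gap for ENCOMPASS.

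5. *The brief intervention would not look harmful.* A reader might infer that the risk split alone could make it appear so. The drift is at most about 1.1 standard errors at n = 116, and a modest decline after arrest would outweigh it. That reading is not supported.

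Risk level determination also still mentions randomisation between two brief interventions. Even if that took place, it would supply no comparator for high-risk youth.

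**Conclusion.** The point holds in this form: the design cannot support an effectiveness statement about ENCOMPASS drawn from change in use, because there is no comparator and selection shares both its construct and its visit with the starting value. That follows from the text and needs no simulation.

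The size is illustrative. Under zero effect, n = 12 and r between 0.5 and 0.9, a significant fall occurs in about 7% to 41% of trials with c between 0.4 and 0.6, and in 24% to 88% with selection purely on use, against 2.5%. These figures assume normality, alpha 0.05, a top-10% cut and a paired test. The direction of any further change after arrest is not settled by the documents. For the brief intervention, selection bias is minor, but its single-group change is equally uncontrolled.

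**What to change.** In the abstract (Methods/design), Overview of study design and objectives, Preliminary analyses, Analyses and Discussion, describe single-group ENCOMPASS and brief-intervention results as change from baseline that cannot be attributed to the intervention. Report them as estimates with 95% confidence intervals and draw no effectiveness conclusion from their p-values. State that within-group change will not be carried forward as the treatment effect size for the larger study. Add regression to the mean and the lack of a comparator to Limitations.

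Setting a fall expected from selection alone beside the result, using the study's own correlation, is not advised. It would come from treated youth, so it mixes selection with any treatment effect. At n = 12 an observed correlation of 0.6 has a 95% interval of about 0.04 to 0.87 (Fisher z: 0.693 ± 1.96/3).

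The cost is wording and a more modest stated conclusion. No new data and no change to care are needed.

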**Discussion:**

Findings have the potential to improve screening and intervention services for YIJJ.

## Background

Youth involved in the juvenile justice system (YIJJ) present with substance use disorders (SUDs) and mental health problems at significantly higher rates than non-offending peers in the community [1–4]. Though estimates vary by population characteristics and assessment criteria [5], up to 80% of justice-involved youth report lifetime substance use; moreover, between up to 40% of justice-involved youth meet criteria for a SUD [3, 6, 7], and a significant portion of youth offenders suffer multiple comorbid mental health disorders and SUDs [2, 8]. Arrested youth also initiate substance use earlier than other adolescents, which increases risk of developing more severe substance use problems [5]. While cannabis and alcohol are the most widely used substances among both justice-involved and non-justice involved adolescents, justice-involved youth use more dangerous drugs, such as opioids, at higher rates compared to their non-justice-involved peers [9]. Despite this significant behavioral health burden, YIJJ access behavioral health (mental health and substance use) services at low rates, and at much lower rates than non-offending peers [10]. For example, in one large scale study of youth offenders, well under 20% of detained youth were engaged in behavioral health treatment at 60 days following release to the community [6]. Effective evidence-based interventions targeting behavioral health among YIJJ exist [11–17]; however, only a relatively small number of communities have access to these programs, contributing to the findings that of the small sample of YIJJ who engage in behavioral health treatment, most do not receive evidence-based treatment [14]. The goal of this manuscript is to describe a protocol to implement substance use screening in juvenile justice settings and evidence-based substance use interventions in community mental health centers targeting YIJJ.

### Barriers to engagement in substance use and behavioral health treatment

There are multiple barriers that prevent YIJJ from engaging in substance use—and other behavioral health—treatment; however, for the purposes of the proposed study, we highlight barriers at the level of the juvenile justice system related to screening and identification of YIJJ in need of services, and barriers at the community level in regards to providing appropriate and evidence-based services.

#### Substance use screening in the juvenile justice system

First, there is a lack of systematic mental health and substance use screening in the juvenile justice system [18]. Given the high rates of substance use and mental health problems among YIJJ, as well as the higher risk of recidivism among YIJJ with substance use and mental health problems, screening and identifying those in need of services is an important task for juvenile justice staff [6, 18–20]. Although juvenile probation officers (JPO) typically function as gatekeepers who help connect YIJJ with appropriate services, there is often a significant lag time between YIJJ’s release from detention and their first contact with a JPO, which leads to delays in service connection and engagement. Moreover, arrest and detention can be viewed as a “crisis event” for youth during which time their motivation for seeking behavioral health services is high; therefore, screening and identification of service needs and connection to services is crucial during the initial intake period following arrest [21]. Thus, we propose to implement universal substance use screening in juvenile justice settings during initial intake following arrest in order to increase identification of YIJJ in need of services and in turn increase referral and connection to appropriate services in community-based settings.

### Evidence-based substance use interventions in community mental health centers

Although evidence-based interventions (EBI) for substance use targeting YIJJ exist [22], high-quality EBIs often are not available in community mental health centers (CMHC). In addition to lack of dissemination and implementation of EBIs in CMHCs, there is also a shortage of behavioral health providers and clinicians in community-based settings to provide these services, and caseloads often are too large to implement intensive treatments [23, 24]. Therefore, there is a need for implementation of cost-effective, feasible EBIs that appropriately address substance use with YIJJ in community-based settings.

In accordance with the substance use care continuum [25], we propose to implement both brief and more comprehensive substance use interventions in CMHCs in order to address the heterogeneity in substance use severity. Implementing EBIs for varying levels of substance use risk ensures that lower risk individuals are not assigned to a higher level of care than necessary, as this creates a burden on the individual receiving treatment and reduces treatment engagement. Further, brief interventions are also cost-effective, and since they can be implemented by professionals with a range of training background, this limits the burden on community-based behavioral health providers by distributing workload across all personnel [26].

We propose to examine the effectiveness of an individual-based brief intervention, Teen Intervene [27, 28], which is based in motivational interviewing and have been show to effectively reduce mild to moderate substance use among adolescents and, specifically, among YIJJ [29]. Teen Intervene is a manualized, three- to six-session individual-based treatment targeting youth substance use that utilizes principles of motivational interviewing, cognitive-behavioral therapy, and self-change principles [27, 28]. Teen Intervene has been shown to reduce substance use and increase motivation to change substance use among adolescents [28] and court-involved adolescents [29] with mild to moderate substance use.

In addition to implementing a brief intervention, we also will implement a more intensive, comprehensive EBI for YIJJ with more severe substance use problems. There are several empirically supported outpatient treatment options for adolescents with problematic substance use and more severe substance use disorders [30], including cognitive behavioral therapy (CBT), motivational enhancement treatment (MET), and contingency management (CM). Moreover, these EBIs have been shown to be effective in reducing substance use when delivered in combination, such as MET combined with CBT and contingency management (MET/CBT + CM). One such integrated intervention model, ENCOMPASS, is a manualized outpatient intervention that combines MET/CBT + CM and pharmacotherapy to treat adolescents with co-occurring substance use and common mental health disorders (e.g., depression, attention-deficit/hyperactivity disorder). ENCOMPASS has been implemented in three randomized controlled clinical trials in youth who met criteria for an average of three substance use disorders and two to three psychiatric disorders [31–33]. Collectively, results demonstrated significant reduction in both substance use and mental health disorder severity—with outcomes comparable or superior to outcomes from trials for separate or sequential substance use or mental health treatments. ENCOMPASS also entails pharmacotherapy, which may include medication assisted treatment for more severe substance use, such as opioid use or alcohol. YIJJ are more likely to use opioids and have more severe substance use problems compared to non-offending peers [9]; thus, implementation of EBIs that include medication assisted treatment is important given the effectiveness of medication assisted treatment for adolescents with opioid use disorder [34–36].

